#### Independent variables

##### Patient variables

• Socio-demographic characteristics: province, sex, age, marital status (married/living with partner, separated, widowed, divorced or single), employment status (employed, unemployed/looking for a job, retired, unable to work, looking after family or home, in full-time education, and other), educational level (beyond secondary education, secondary education, primary education and incomplete primary education/illiterate), owner-occupier of an accommodation (owner, mortgage, rented, and other), living alone or with others [62].

• Anxiety disorders using the anxiety section of the Primary Care Evaluation of Mental Disorders (PRIME-MD) [63]. The Spanish version of the PRIME-MD can classify patients who test positive for panic attack, generalized anxiety disorder and other anxiety disorders [64]. We will use a dichotomous anxiety variable to indicate when any of the three diagnoses of anxiety are present in a given patient.

• Controls, demands and rewards for unpaid work, using an adapted 7 item version of the job content instrument [65]. From the sum of the seven items, the variable is categorized in 3 (satisfied, dissatisfied and very dissatisfied).This questionnaire has previously shown good validity and reliability in Spain [62].

• Satisfied with living together at home (5-Likert response options).

• A lifetime screen for depression based on the first two questions of the CIDI [66].

• Childhood experiences of physical abuse (5-Likert response options) [67].

• Presence of serious physical, psychological or substance misuse problems, or any serious disability, in persons who are close friends or relations of participants. These questions can be used as 4 different items (yes/no) or as an ordinal variable (summation of the 4 questions).

• Whether the participant’s mother committed suicide (yes/no) [68].

• Perception of safety inside and outside the home using a question from the Health Surveys for England with 5-Likert response options [69].

• Experiences of discrimination on the grounds of sex, age, ethnicity, appearance, disability, sexual orientation, and others using 7 questions (yes/no) from a European study [70]. The answers to these seven items can also be joined in an ordinal variable.

• Taking medication for anxiety, depression or stress in the previous 6 months (yes/no).

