• Probability of the onset of major depression at 12 months, obtained from the equation “predictD-Spain”, which has been previously validated [34] and is derived from a combination of some of the above variables.

We will assess all these variables and questionnaires at baseline, 6, 12 and 18 months. The test–retest reliability of questions used in the predictD studies has been reported previously [62,71].

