How patients are informed about their risk of becoming ill (cardiovascular events, hip fractures…) determines the outcome of prevention efforts [98,99]. In the same qualitative study as mentioned above, we found that primary care patients are pleased to be informed of their risk for depression [97]. Communicating with patients about their level and risk profile for depression is very new as until now there have been no validated risk algorithms to predict its onset [33,34]. This is also “*the starting component*”, which will activate the other components of the intervention. Each FP will receive (at baseline, 6 and 12 months) a report with the information on risk from each of 24 patients not depressed at baseline (belonging to their usual patient list) who will be randomly selected and will provide informed consent to participate in the study. This report will include the likelihood of becoming depressed at 12 months and the patients’ responses to each of the risk factors included in the predictD-Spain equation [34]. An example of a report of a patient who has 24.4% of becoming depressed at 12 months is shown in Figure 1.

If a patient has a moderate or high risk level (2nd or 3rd tertile), the FP will arrange an appointment with the patient aiming to communicate his/her risk of depression. If a patient has a low risk (1st tertile), the FP will have the option to report by telephone or face to face depending on the patient’s preferences. If a visit is scheduled, this will last approximately 10 minutes. This process of transmitting risk information will be held at baseline, 6 and 12 months. Reports will not include information about major depression diagnosis by CIDI at 6 and 12 months; although we will recommend that FPs screen for depression if the risk of depression was moderate or high at 6 and 12 months. FPs will write down on the problem list (clinical chart) the label “*predictD*” in order to remind them on opening their clinical charts that patients are included in the program predictD to prevent depression. This will help to ensure that when patients see their FPs, regardless of the reason for the consultation, doctors will take into account the information on their risk of depression if applicable.

3) *Building up a tailored bio-psycho-family-social intervention to prevent depression by family physicians*

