### Quality control of the intervention

In order to control the satisfaction and adherence to the intervention we will undertake two quality controls. The first one will be from a subjective focus. After each interview to inform patients about their risk of depression, the FPs will have to answer four questions: Have I written the label “predictD” in the clinical chart? (yes/no); what is my level of satisfaction with this interview to report the risk of depression? (5-Likert response options); would I change anything in this interview? (open answer); and observations (open answer). All patients will be asked about their overall satisfaction with their doctor (5-Likert response options); and only patients receiving the intervention will respond to the question “What is your level of satisfaction with the last interview in which your doctor informed you about your risk of depression?” (5-Likert-5 response options or “I was not informed”). The second is from an objective focus: we will review the clinical charts to confirm that FPs have included the label “predictD” on the problem list and we will also collect the number and content of visits related to the intervention.

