### Side effects of the intervention

It is possible that some patients will react with fear or worry when receiving information about their level and risk profile of depression, especially apprehensive patients or those that already have a high level of anxiety. If a patient does not want to receive this information he/she will not sign the consent and therefore will be excluded from the study. This will be valid for each evaluation point. As stated in component 5 of the intervention, we will train FPs to support those patients excessively worried by the information given. FPs are obliged to report any side effect that occurs during the intervention. We will also evaluate the impact of the predictD-CCRT intervention on anxiety symptoms through measurements of the PRIME-MD [63,64] at each evaluation point of the follow-up.

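### Fear or worry on being told one's risk has no structured record at the disclosure, and the next anxiety measure comes about six months later, so brief distress may go unrecorded

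*Protocol article*

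**What the plan says.** The section Side effects of the intervention states the harm in view: "It is possible that some patients will react with fear or worry when receiving information about their level and risk profile of depression". It gives two ways of finding it. The first is a duty on the physician: "FPs are obliged to report any side effect that occurs during the intervention". The second is a questionnaire: "We will also evaluate the impact of the predictD-CCRT intervention on anxiety symptoms through measurements of the PRIME-MD", at each evaluation point.

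On timing, the description of the component on communicating risk says: "This process of transmitting risk information will be held at baseline, 6 and 12 months". The list of patient variables, which includes the PRIME-MD anxiety section, ends: "We will assess all these variables and questionnaires at baseline, 6, 12 and 18 months". The same list fixes how PRIME-MD is scored: "We will use a dichotomous anxiety variable to indicate when any of the three diagnoses of anxiety are present in a given patient".

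The section Quality control of the intervention describes a form: "After each interview to inform patients about their risk of depression, the FPs will have to answer four questions". The questions cover whether the chart label was written, the FP's satisfaction with the interview, what the FP would change (open), and observations (open). Intervention patients are asked how satisfied they were with the last risk interview. Charts are reviewed for the number and content of visits related to the intervention.

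**The concern.** The harm that the protocol names is a reaction at the moment of hearing the risk. The only questionnaire measure of anxiety is taken on the trial's six-monthly schedule and recorded as presence or absence of a diagnosis. Two instruments already address the disclosure itself, the FP form and the patient's question on the last interview, and neither asks how the patient reacted.

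This matters because the intervention is universal. People at low risk are told their risk too, possibly by telephone. The article also reports from its own qualitative work that FPs feared causing distress by disclosing risk. A reader of the results will want to know how often disclosure upset people, as a proportion of disclosures made. A small number of unsolicited reports would not answer that.

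**Working it through.** The article gives no figure for side effects, so there is nothing to reproduce. The check is one of timing and of what each instrument asks.

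**Order of interview and disclosure.** The FP's risk report is described thus: "This report will include the likelihood of becoming depressed at 12 months and the patients’ responses to each of the risk factors". Those answers come from the research interview, so the interview at a given month must come before that month's disclosure. This is inferred from how the report is built, since the article gives no exact dates.

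**Gap from disclosure to next PRIME-MD.** Disclosure months are 0, 6 and 12. PRIME-MD months are 0, 6, 12 and 18.

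| Disclosure (month) | Next PRIME-MD (month) | Gap (months) |
|---|---|---|
| 0 | 6 | 6 − 0 = 6 |
| 6 | 12 | 12 − 6 = 6 |
| 12 | 18 | 18 − 12 = 6 |

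The actual gap is shorter by whatever delay there is between interview and disclosure, so about six months is the right description.

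**What PRIME-MD can show.** It is a yes/no variable for any of three anxiety diagnoses, taken in both arms. An arm difference at 6, 12 or 18 months is the net effect of the whole intervention on anxiety that is present then. Worry that has settled by the next interview does not appear in it.

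**What is asked near the disclosure.**

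| Source | Asks about the patient's reaction? |
|---|---|
| FP form, chart label | No |
| FP form, FP's satisfaction | No |
| FP form, what to change (open) | Not asked; could be written in |
| FP form, observations (open) | Not asked; could be written in |
| Patient question on last risk interview | No; satisfaction only |
| FP duty to report side effects | Covers it; no prompt described |
| Chart review of visit content | Only if a related visit took place and was noted |

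On the form, 0 of 4 questions ask about the reaction, and 2 of 4 are open answers that could hold it. A blank open answer can mean that the patient was untroubled or that nothing was written down.

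**Number of disclosures.** With 1643 patients planned in the intervention arm and three disclosures each, 1643 × 3 = 4929. This is a ceiling before attrition, and patients may decline the information at any evaluation point.

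**The case against.** The strongest reply is that the article makes side-effect reporting mandatory. It places that duty on FPs who conduct the disclosure and who are trained to listen for its impact and to support patients who become excessively worried. The four-question form exists to monitor satisfaction and adherence; side effects have their own section, and the reporting form behind the duty may be in the full protocol, which is not shown. PRIME-MD is offered as an additional measure of anxiety symptoms, not as a measure of the immediate reaction. It is collected by interviewers not informed of the arm, which makes it a sound randomised comparison.

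Most of this stands. The absence of a side-effect form from a journal article is not an error, and PRIME-MD is suitable for lasting anxiety. The reply does not remove the narrower point. A duty to report is not a prompt to ask, and the form completed after each interview, whose items the article lists in full, does not ask.

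Three stronger readings are tempting and are not supported:

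- A reader might infer that harm will be under-counted. No reporting rate or event rate is given, so the document shows a risk and not its size.
- A reader might infer that reactions starting after the visit cannot be detected at all. The chart review and the FP's duty could catch some of them.
- A reader might infer that upset patients will be lost before the next PRIME-MD, because anyone not wanting the information is excluded and this applies at each evaluation point. The article does not say how many would leave, or whether they would be interviewed first.

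**Conclusion.** The point holds in a limited form. As described, detection of immediate fear or worry relies on reporting by the unblinded FP who delivers the information, helped by free text and chart review. The next anxiety measure is about six months away and is a diagnosis, so it bears on lasting anxiety only. Under-reporting of brief distress is a plausible risk whose size cannot be computed from the document. The firmer conclusion is that these instruments cannot separate no reaction from a reaction not recorded, so they yield no solicited rate over the planned maximum of 4929 disclosures.

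This rests on two assumptions: that each interview precedes its disclosure, and that the full protocol does not already hold a structured reaction item. If it does, the point falls away. The finding is a low-cost improvement to harm data that cannot be recovered later. It is not a contradiction in the plan and does not affect the primary analysis.

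**What to change.** Add one mandatory closed item to the form the FP already completes after each disclosure: patient reacted with fear or worry, none / mild / marked. Require it for telephone disclosures too. Report the rate with all completed disclosures as denominator, and show the number of missing forms. State that PRIME-MD will be interpreted as a between-arm measure of lasting anxiety.

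A matching patient item could be added beside the existing question on the last risk interview. It should be treated as supplementary, because if asked at the scheduled evaluations it depends on recall over about six months.

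The cost is a few seconds per contact. With 35 × 2 = 70 intervention FPs, the ceiling is 4929 / 70 ≈ 70 entries per FP over the trial. No extra visit or staff is needed. The rating would still be made by the unblinded FP, so it improves completeness without removing observer bias, and the published side-effect rate may look less favourable than one based on unprompted reports.

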### The intervention for the control group

Patients in the control group will receive “usual care”; that is, the kind of care that FPs usually provide when they are unaware of the risk profile for depression in the patients. This means explicitly that the patients and FPs in the control groups will not be informed about the risk profile at any point. FPs in the control group will not receive the training workshop.

## Discussion

### Ethical considerations

FPs who do not meet exclusion criteria will be asked to sign an informed consent form before health centers are allocated to the control or intervention group. Once the health centers are randomly assigned to the control or intervention groups, selected patients who do not meet exclusion criteria in the health centers of the control group will be asked for consent to follow-up and in the intervention group to receive the intervention and to follow-up. In each health center a research assistant will ask participants to sign informed consent forms. In brief, participants in the intervention group will be informed about the purpose of the trial, the expected duration of their participation, trial procedures, foreseeable risks or inconveniences, expected benefits, whom to contact for further information, their rights as participants, and that their participation is voluntary and that they may refuse to participate or withdraw from the trial at any time, without penalty or loss of benefits. Since the identity of patients will not be known at the time when randomization of health centers is to be carried out, it will not be possible to seek their consent in advance of randomization. Nevertheless, FPs will provide consent to participate in the trial; moreover, none of them will be involved as a researcher in this study, so there should not in theory be a conflict of interest. In view of the fact that so far there is no evidence that the new intervention being evaluated in this study is effective, and given that it is generally the responsibility of FPs to put the medical interests of their patients above all other considerations, this may be an appropriate choice [109].

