#### Family physicians

In each participating health center we will exclude those FPs who are unfamiliar with using the clinical chart or are planning to change their place of work in the next 18 months. We shall then invite all remaining FPs to participate and from those who agree, randomly select two per center (before randomization of centers) using closed and opaque envelopes selected by an independent person from the research group. This will mean 140 FPs will participate in the trial.

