#### Patients

Patients belonging to the 140 FPs will be selected using a systematic random sampling, each 4–6 patients, from the FPs’ appointment lists at random starting points for each day. This will be done by an assistant researcher for each health center. The list of selected patients will be given every day to the family physician (FP) before starting to see patients. FPs will check the selected patients to see if they meet any of the following exclusion criteria: age under 18 or over 75 years; inability to understand or speak Spanish; severe mental disorder (psychosis, bipolar, personality disorder,…); cognitive impairment; terminal illness; the patient is scheduled to be out of the city more than four months during the 18 months of the follow-up; and persons (representatives) who attend the surgery on behalf of the person who has the appointment. The FPs will introduce the study to the selected not excluded patients and will request permission before contacting the assistant researcher. Patients who refuse to participate will not be replaced, prolonging the days of recruitment to achieve 26–27 patients for each FP. Those who give informed consent will undertake a research interview within two weeks with the Composite International Diagnostic Interview (CIDI) in order to detect the presence of major depression. Patients with a diagnosis of current major depression will also be excluded from the trial. The exclusion criteria for health centers, FPs and patients are shown in Table 1.

**Table 1 T1:** Exclusion criteria of the predictD-CCRT study

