### Masking

In trials that evaluate psychosocial interventions it is not possible for professionals who provide the new intervention or for patients who receive it to be blind to it [53]. However, in our trial those who assess outcomes (interviewers) will be different and independent from those who provide the intervention (FPs). Moreover, the interviewers will be not informed of the patient’s status in the control or intervention group. Those who perform statistical analyses will also be blind to the intervention and control codes.

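### Patients are screened, invited and asked for consent after their centre is allocated, with a different consent in each arm, so entry and retention can depend on arm

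*Protocol article*

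**What the plan says.** All places are in the protocol article.

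- **Order.** FPs are drawn and give consent before centres are randomised (Family physicians; Ethical considerations). Patients come later: "Once the health centers are randomly assigned to the control or intervention groups, selected patients who do not meet exclusion criteria" are then asked for consent. The reason given is that their identity is not known at that time, so "it will not be possible to seek their consent in advance of randomization" (Ethical considerations).
- **Who screens and invites.** "FPs will check the selected patients to see if they meet any of the following exclusion criteria", and "The FPs will introduce the study to the selected not excluded patients and will request permission before contacting the assistant researcher" (Patients).
- **Who takes consent.** "In each health center a research assistant will ask participants to sign informed consent forms" (Ethical considerations).
- **What is consented to.** Control patients "will be asked for consent to follow-up and in the intervention group to receive the intervention and to follow-up" (Ethical considerations): the control request covers follow-up only, and the intervention request covers both.
- **Exit tied to the intervention.** A patient who does not want the risk information does not sign and is excluded, and this applies again at each evaluation point (Side effects of the intervention). Control patients are never told their risk (The intervention for the control group), so they never face that choice.
- **Masking.** "it is not possible for professionals who provide the new intervention or for patients who receive it to be blind to it". Interviewers are not told the patient's arm (Masking).
- **Safeguards.** An assistant researcher draws a systematic random sample from appointment lists (Patients). The model adjusts for the baseline predictD score and, where appropriate, for unbalanced variables (Regression models). Imbalance is checked at centre, FP and patient level (Strengths and limitations).

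**The concern.** Cluster randomisation makes the arms comparable in centres and FPs, both fixed beforehand. It makes them comparable in patients only if the route into the trial is the same in both arms. Here the request put to the patient differs by arm, and so does the task the FP takes on by recruiting.

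The protocol gives its own reasons to expect this to matter. It anticipates fear or worry at risk information, particularly in patients who are already anxious (Side effects of the intervention). Its earlier qualitative study found FPs reluctant to disclose risk, afraid of causing distress and short of time (component 1 of the intervention). Some exclusions, such as severe mental disorder and cognitive impairment, leave room for judgement. If the patients lost through these routes differ in their risk of depression, the primary comparison carries a difference that the intervention did not cause.

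The same exit operates during follow-up, where patients can leave the intervention arm for a reason that does not exist in the control arm.

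**Working it through.** **1. Does entry depend on arm?** Recruitment follows allocation, the request differs by arm, and one reason for exclusion exists in only one arm. That is enough for entry to depend on arm, even if every FP screens impartially.

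**2. Do the safeguards close the gap?**
- Systematic sampling protects who is listed, not who is screened in or agrees.
- The CIDI exclusion is assessed by interviewers not told the arm, but it acts only on patients who have already agreed.
- The fixed adjuster is the predictD score. It includes the SF-12 mental score and medication for stress, anxiety or depression, but no anxiety diagnosis (The 'predictD' algorithm). Other variables enter only if measured and found unbalanced.
- Inverse probability weighting models remaining in follow-up, and multiple imputation is offered against attrition. Neither corrects who enters. They can address later exits only as far as the recorded variables explain them.
- Recruitment is prolonged until each FP reaches 26–27 patients, so differential refusal need not show in the arm sizes.

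**3. How large could it be?** The protocol gives no figure for this, so what follows is an illustration. From the Sample size section: control incidence 12%, target difference 5 points. Assumed: no true effect, and a share f of eligible patients who decline only in the intervention arm, with RR times the risk of the others. Incidence among those who enter is then x = 0.12 / (f × RR + 1 − f), and the false difference is 0.12 − x.

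| f | RR | x | False benefit (points) | Share of 5 points |
|---|---|---|---|---|
| 5% | 1.5 | 0.12/1.025 = 11.7% | 0.3 | 6% |
| 10% | 2 | 0.12/1.10 = 10.9% | 1.1 | 22% |
| 10% | 3 | 0.12/1.20 = 10.0% | 2.0 | 40% |
| 20% | 2 | 0.12/1.20 = 10.0% | 2.0 | 40% |
| 20% | 3 | 0.12/1.40 = 8.6% | 3.4 | 69% |
| 10% | 0.5 | 0.12/0.95 = 12.6% | −0.6 | −13% |

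The last row shows the reversal when decliners are at lower risk.

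**4. Against sampling error.** The stated design effect reproduces: 1 + (48 − 1) × 0.06 = 3.82, and 430 × 3.82 = 1642.6, or 1643 per arm. The effective size is 1643/3.82 = 430 per arm. With 12% against 11%, the standard error is √[(0.12 × 0.88 + 0.11 × 0.89)/430] = 2.2 points. At a two-sided 5% level (the protocol does not state the sidedness), a false difference of 1 point raises the rejection rate under no effect to about 7.5%, and one of 2 points to about 15.5%.

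**5. Effect of adjustment.** These are crude differences. If adjustment removed half the log risk ratio (an assumption), the 10%, RR = 2 case has a residual RR of √2 = 1.41, and 0.12/(0.10 × 1.41 + 0.90) = 11.5%, a false benefit of about 0.5 points.

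**The case against.** The strongest case is that this is an openly defended cluster design with real safeguards. FPs do not choose whom to consider. Most exclusions are factual, such as age, language or absence from the city. Since each FP recruits to a fixed target, screening out one patient does not reduce the number of risk interviews, which weakens the workload motive. The predictD score has a reported C-index of 0.82, and anxiety is measured at baseline and available for adjustment. The limitations section says that balance at FP and patient level is not guaranteed, and names patient refusal as a possible selection bias. All of this stands and lowers the likely size. None of it makes the request the same in both arms, and the refusal discussion is general: it sits beside external validity and does not name recruitment that differs by arm.

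A reader might infer more than the text supports in three places:
- **That the allocated FP obtains consent.** A research assistant takes the signature; the FP screens and invites.
- **That FPs are shown to know their arm when screening.** This is a reasonable inference from recruitment after allocation, arm-specific consent and unmasked providers. It is not stated, and the timing of the workshop relative to recruitment is not given.
- **That the sentence on prior consent is false.** Under the chosen order it is true. It describes that order rather than showing that no other was possible.

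There is also a fair objection to the obvious remedy. A single consent form describing both arms would tell control patients about the intervention, and the protocol relies on their consenting to follow-up only as a reason why they are less likely to change behaviour. With five centres per arm in each city, opening envelopes centre by centre would also make the last allocations predictable. The fix has to avoid both.

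**Conclusion.** The point holds. Who enters and who stays can depend on arm, and the planned analysis corrects this only through measured variables. It is a weakness worth removing, not proof of a biased result.

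The direction is unknown: anxious patients may avoid risk information, or low-risk patients may see no use in it, and the protocol's own qualitative work reports that patients were pleased to be told. A reader might take the 1.1 points as the expected bias in favour of the intervention. The documents do not support that, because the share declining and their relative risk are assumed and the figure precedes adjustment. Across the harmful-direction scenarios above, the crude false benefit runs from 0.3 to 3.4 points. Nor does it follow that randomisation gives no protection: centres and FPs remain protected.

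**What to change.** 1. Withhold allocation from FPs, research assistants and patients until all ten centres in a city have sampled, screened, consented and baseline-interviewed their patients. Then open that city's envelopes together and run the workshop in its intervention centres.
2. Before disclosure, use the same consent to baseline interview and follow-up in both arms. After disclosure, ask intervention patients separately whether they want the risk information. Control patients are then not told about the intervention.
3. Amend Side effects of the intervention so that patients who decline the risk information, at baseline or later, stay in follow-up unless they withdraw from it, and stay in the intention-to-treat analysis.
4. Amend the sentence in Ethical considerations to say that prior consent is impossible only under the chosen order, and name differential recruitment by arm in Strengths and limitations.

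**Cost.** A protocol and consent amendment, and a delay between baseline and the start of the intervention. The documents do not allow the length of that delay to be fixed. It slightly dilutes exposure in the first 6-month period. It is limited because the risk report needs the baseline answers, so no patient's intervention can begin before the baseline interview in any case.
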